#### Comprehensive component

##### Semi-structured interviews

Semi-structured interviews allow the respondent to speak while the interview is focused on the subject of the study (the opposition) [33]. They are conducted using an interview matrix that presents the topics that will be discussed with the interviewee. When the topics are determined in advance, their order and presentation format are decided by the interviewer. The researcher has a series of relatively open-ended guiding questions directly based on the themes to be covered (see Table 1) for which he/she wishes to obtain information. Semi-directed interview guides are developed and tested in consultation between the investigating physician and researchers involved in the project. They are adapted and improved during the study to explore all the themes that are essential to understand the situation.

During an interview, the relationship between the interviewer and the subject is based on trust, respect, and empathy. The subject must be comfortable, knowing that the interview is a privileged moment, so that he/she can express his/her experience, his/her journey, and his/her representations. He/she must perceive that the researcher is there to listen to him/her. The researcher’s listening position is essential to allow the respondent to tell his/her subjective experience and to move away from what he/she can socially consider as expected by the researcher [34].

Semi-directed interviews will be recorded with a voice-recorder and fully transcribed anonymously and confidentially. In the information note and consent, the patient, family member, and caregiver will be informed of this modality.

The objective of the semi-directive interview with the patient is to understand the meaning or justification for this opposition. The objective of the meeting with the family member and the usual caregiver (institutional caregivers, if applicable, or primary caregiver at home) is to understand the positioning of this opposition with the patient’s previous expressions, to collect their analysis or interpretation, and to cross-reference the elements reported by the patient, family members, and caregivers.

##### Medical survey

General practitioners are a research population that is difficult to reach in qualitative research because of time constraints resulting from their practice. The telephone questionnaire completed with the family physician will take into account professional requirements and their limited availability and allows to collect information on the patient’s prior positioning concerning any limitation of care. The family physician will report his/her analysis or interpretation of the patient’s positioning, which will be cross-referenced with other elements collected during interviews with the patient, his/her relatives, and hospital carers. Differences in perceptions will be used to bring out a more comprehensive meaning of the opposition that will be reported for each patient.

The use of qualitative telephone surveys (structured interviews) makes it possible to partially overcome availability constraints, and thus integrate into this study the point of view of the general practitioner, which is essential for the overall understanding of the patient’s positioning in opposition to care, especially since phone exchanges are usual in these circumstances, and primary practitioners appreciate when they are included in the discussion surrounding these situations.

##### Observation of hospital collegial meetings

It is during collegial discussions that decisions are made in response to patients’ opposition to care. During these discussions, and as part of a team dynamic, each caregiver expresses his/her opinion about the patient’s situation and explains the possible justifications for the limitation of diagnostic or therapeutic procedures. The objectives of collegial meetings are to have an overview of the patient’s positioning and discuss the different points of view. The objective of observing a hospital meeting concerning the complex management of the opposition to care is to evaluate the significance given to the patient’s positioning in acute contexts by medical and paramedical teams. Indeed, this opposition potentially challenges the foundations of hospital-based, active, and performance-based medicine.

The observation will be conducted by a researcher (psychologist or sociologist). In order not to restrict exchanges, and thus facilitate the free expression of the teams, it is decided not to record these exchanges, and notes will be taken by the researchers to record the dynamics of the exchanges, the positions, and the questions raised by caregivers.

### Data analysis

#### Statistical analysis of epidemiological data

Analyses for the quantitative component are based on the data that will be extracted from medical records and descriptive statistics calculated based on this data.

The data of the reference population for statistics on prevalence and comparisons with the general population will be determined according to results obtained in a survey of professional practices conducted within the same geriatrics service. An anonymized database was therefore created to compile the medical and socio-demographic data of 60 patients that were seen in this ward for 1 month. These patients are representative of the population that receives health services in this hospital, which allows comparisons with the study group.

A descriptive analysis of the data will be conducted. Patient characteristics will be described using mean and standard deviation (SD) or median and interquartile range (IQ) for quantitative variables and using counts and percentages for qualitative variables. Variables will be compared using either the chi-square test or Student’s test. A difference with a *p* less than 0.05 will be considered significant. The R software will be used for these analyses.

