A quantitative study seems necessary to quantify and better understand the parameters associated with situations involving opposition to diagnostic and therapeutic procedures. Although these events are often mentioned in medical literature, they are not documented or compiled in hospital records. Epidemiological studies must be associated with qualitative and comprehensive analyses of events to ensure an in-depth understanding of the opposition expressed by older patients. Is this opposition linked to a distorted and negative representation by patients of the proposed diagnostic or therapeutic procedure? In older people with a certain degree of delirium and/or cognitive deterioration, treatment may be perceived as a threat, intrusion, coercion, obstruction, violence, or even aggression. It is therefore conceivable that some intrusive procedures may be refused. Is this opposition an expression of a desire to control one’s own life until death? Is it not the ultimate expression of the existence of oneself, the expression of an ability to decide for and by oneself, in a world characterized by several constraints and dependence for all acts of daily life? Is this opposition expressing a feeling of indignity experienced in a societal context, or a reaction to ageist tendencies [28, 29] that can generate a sense of social uselessness among the older population? The qualitative component of the present study also contributes to the exploration of interactions between doctors, carers, and relatives confronted with patient opposition; the functioning of collegial meetings and decision-making methods are also addressed to better understand some consequences of the dilemma that arises in cases of opposition to diagnostic or treatment in older patients.

In order to answer these questions and verify the aforementioned hypotheses, it is necessary, in view of the specificities of opposition to medical care and target population (older people, including persons with neurocognitive disorders), to carry out a pilot study beforehand, with the following specific objectives:
To verify the applicability of the proposed definition of opposition to medical care and its reproducibilityIdentify the proportion of patients expressing opposition to medical care according to the proposed definitionIdentify the key elements to be included in the qualitative interview, based on a preliminary interview grid.

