### Study objectives

Epidemiological component: In the epidemiological survey, the objective will be to identify and establish the frequency of situations in which patients will express opposition to treatment or diagnostic procedures. The data will be obtained in the acute geriatric ward of a French university hospital, over 1 year.Comprehensive component: During the semi-structured interviews with carers and relatives involved in the epidemiological component, the objective will be to identify, describe, and understand the meaning of the opposition to treatment or diagnostic procedures expressed by patients included in the study (see below).

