### Population and duration of the study

Patients over 75 years of age who will oppose diagnostic or therapeutic procedures during hospitalization and who will be hospitalized in the acute geriatric ward of a French university hospital will be included in this study. The acute geriatric care department comprises 54 hospitalization beds spread over 2 sections, including 6 geriatric intensive care beds. Medical care is provided with a ratio of one doctor and one intern for every 12 patients in conventional beds and 1 for every 6 patients in the geriatric intensive care unit.

To obtain an exhaustive overview of this population, the epidemiological data collection will involve a standardized survey that includes questions on descriptive characteristics of patients, which will be reported at the time of admission and during a follow-up in geriatric hospital services (collection of medical history, treatments, medico-social data, standardized geriatric assessment). A 1-year recruitment period will be used in this study. Among the patients that will present opposition to treatment or diagnostic procedures, we will select patients that can be interviewed (i.e., without cognitive impairment or with mild to moderate neurocognitive disorders which are not predominantly phasic) for the comprehensive (qualitative) component of this study. It is anticipated that recruitment for interviews could be difficult in this population, and the inclusion period for the second component is 2.5 years. The epidemiological data of patients included in the second year of the comprehensive component will be added to the initial data to allow comparisons between the groups participating in the two components. We will thus verify that for the population included in the comprehensive component, the characteristics of the opposition are similar to those of the overall study population.

The total duration of the study will therefore be 30 months.

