### Data collection strategies

#### Recruitment

This study aims to investigate opposition situations. To make a rigorous analysis, it seems necessary to do an exhaustive census of opposition situations. In that way, we will quantify the number of situations in which there is opposition to diagnostic or therapeutic procedures handled in the department for 1 year.

Given the population and the subject of this study, it is foreseeable that opposition to participation will occur, even though our focus on the refusal and thus the interest and respect for the person’s will can facilitate exchanges. This concern justifies the extension of the comprehensive study for an additional year and a half.

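### The proportion of patients who oppose care has no matching denominator: cases come from a one-year census, the reference from a separate one-month survey of 60 patients

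*Protocol article*

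**What the plan says.** All references are to the protocol article.

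- **Target quantity.** The objectives that close the Hypotheses section include the "proportion of patients expressing opposition to medical care according to the proposed" definition. Study objectives words the epidemiological aim as to "identify and establish the frequency of situations in which patients will express opposition to treatment or diagnostic procedures", over one year.
- **Numerator.** Under Recruitment the study takes an exhaustive census: "we will quantify the number of situations in which there is opposition to diagnostic or therapeutic procedures handled in the department for 1 year". Under Inclusion criteria, only patients who have expressed opposition enter the epidemiological component.
- **Reference.** Statistical analysis of epidemiological data says: "The data of the reference population for statistics on prevalence and comparisons with the general population will be determined according to results obtained in a" practice survey in the same service. It continues: "An anonymized database was therefore created", to "compile the medical and socio-demographic data of 60 patients that were seen in this ward for 1 month".
- **Justification.** The same section adds: "These patients are representative of the population that receives health services in this hospital, which allows comparisons with the study group". It gives no calendar month, sampling method or supporting data.
- **Tests.** Variables are compared by chi-square or Student's test at p < 0.05.
- **Accrual.** Study status reports 33 situations after 20 months, from a start on 1 January 2018.

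**The concern.** A proportion needs a numerator that is a subset of its denominator. Here the numerator is collected over a year from one stream of patients, and the named reference is a different set of patients seen in a single month. Nothing in the article counts the patients who passed through the ward while the census was running. The quantity in the second objective therefore cannot be formed from the stated sources without scaling one month's figure up to the census period.

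The comparisons have the same fault. Cases gathered over a year or more would be tested against an external one-month sample, not against the patients in the same ward and period who did not oppose. A difference could then reflect the month or the way the 60 were chosen, and the design gives no way to tell.

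**Working it through.** The article states no expected prevalence, precision or sample size, so there is no figure to reproduce. The steps below show only how far the answer moves with the stated reference.

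**Inputs from the article:** 60 reference patients in 1 month; census of 1 year; 33 situations in 20 months.

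**Assumptions, for illustration only:** 60 is a complete count of that month's patients; the census was complete in all 20 months; each of the 33 situations is one patient.

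1. *Match of sources.* Numerator: opposing patients in a one-year census. Reference: a one-month survey. The article does not say that the cases are a subset of the 60 or that the survey month falls inside recruitment.

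2. *Error in one month's count.* The exact Poisson 95% interval for a count of 60 is
 - lower: χ²(0.025; 2×60)/2 = 45.8
 - upper: χ²(0.975; 2×61)/2 = 77.2

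3. *Scaling to 20 months.*
 - 45.8 × 20 = 916, and 33/916 = 3.6%
 - 60 × 20 = 1,200, and 33/1,200 = 2.75%
 - 77.2 × 20 = 1,544, and 33/1,544 = 2.1%

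 The denominator's chance error alone moves the estimate by a factor of 3.6/2.1, about 1.7. It comes on top of the ordinary binomial uncertainty (33/1,200 has an exact 95% CI of 1.9% to 3.8%) and before any variation between months. If 60 is only part of the month's patients, the true denominator is larger and the proportion lower, by an amount the article does not allow one to work out.

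4. *Measuring opposition inside the 60 instead.* The article mentions no opposition variable in that database. If there were one, at 2.75% the expected number of cases is 60 × 0.0275 = 1.65. Two cases in 60 would have an exact 95% CI of 0.4% to 11.5%. This route does not rescue the objective.

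5. *Comparisons.* A reference percentage near 50% from 60 patients has a 95% half-width of 1.96 × √(0.25/60) = 12.7 points, before any question of whether the month is typical.

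**The case against.** The best defence is that this is a condensed article on a single-centre pilot. Admission counts might sit in the full protocol, the 60 patients come from the same service, and the database may be meant mainly as a descriptive profile. Part of that stands: the survey can describe case mix approximately, and no number stated in the article is wrong. But the article is not silent on the reference. It names the survey for prevalence statistics as well as for comparisons, and the proportion is an explicit pilot objective.

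A reader might infer more than the text supports:

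- *That the plan would divide the 33 situations by 60, or by one year's worth of the monthly 60.* No section proposes the first, and the second sets a 20-month count against 12 months.
- *That 60 a month is too few for the ward.* "The acute geriatric care department comprises 54 hospitalization beds spread over 2 sections", but the article gives no occupancy, length of stay or admissions and does not say whether 60 is a full count or a sample.
- *That situations are counted against patients.* The section on the comprehensive part uses the two words for the same ten or so cases, so a mismatch of unit is not shown.
- *That the reference includes younger patients, or opposing patients who cannot be removed.* Both are inferences from silence. The article does not give the survey's age range, its month, or whether opposition was recorded.

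The 33 also cannot be taken as a 20-month census. Recruitment limits the exhaustive count to one year, and Population and duration of the study says only that data from patients of the extended comprehensive component are added afterwards.

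**Conclusion.** The concern holds as a mismatch between a stated reference and a stated objective. The one-month survey of 60 is not the population that produced the cases, and no other denominator is given, so the proportion of patients who oppose care cannot be properly estimated as planned.

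The size can only be illustrated: 2.1% to 3.6% from chance error in the monthly count alone, on the three assumptions listed in the working. The real uncertainty is wider if 60 is a sample or the month was unusual. Nothing is lost beyond repair, since the ward's admissions over the census year can be counted afterwards.

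**What to change.** - **Denominator.** Take from the hospital's administrative records all distinct eligible patients (over 75, as in Population and duration of the study) admitted to the same ward in the same 12-month census window. From the reported start date this is 1 January to 31 December 2018.
- **Numerator.** Count distinct patients with at least one qualifying opposition in those 12 months. Later cases stay in the descriptive and qualitative work but do not enter the proportion.
- **Report.** Give the proportion with an exact 95% CI. A rate per 1,000 patient-days is optional.
- **Comparisons.** For variables held administratively (age, sex, stay, outcome), compare opposing with non-opposing patients from that cohort. Keep the 60-patient survey only for variables not held there, labelled as an external one-month sample, and state its month, how patients were selected and whether 60 was a full count.

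The cost is one administrative extract and a rewritten analysis paragraph, with no new patients or visits. The numerator becomes smaller: if accrual was even, about 33 × 12/20 = 20 of the 33 situations would fall in the census year. The interval will be correspondingly wider, but it will belong to a defined population.

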#### Qualitative methodology

Interviews will be conducted until saturation of data and concepts is obtained, i.e., when the inclusion of a new participant no longer provides additional information to the investigation. This is an interactive process where new data are integrated progressively with the analysis of previous data. This integration provides new insights into the work that has been done and helps to plan the next interviews, when they are necessary. If the newly collected data does not bring new information, i.e., when the categories include all the elements of the phenomenon, and the links between the categories are established and validated, data saturation is reached [35].

All interviews and observations collected during team meetings will be transcribed or narrated anonymously and confidentially. Thus, the names of persons and places mentioned in the interview are not included in the transcripts.

It is considered that a rigorous analysis of interviews is only possible if the content of their recording is transcribed in writing. As some written documents will be consulted during the interview, the full transcription includes all verbal, para-verbal, and non-verbal information presented by the interviewee and the interviewer. All statements in the transcription are in the order in which they were stated. Repetitions and speech errors will not be removed from the transcript. Punctuation rules which are essential for the readability of the text (comma, endpoint, suspension point) will, however, be respected. The transcriber will set the rules for transferring from the verbal to the written register in a conventional way, and he/she will comply with them for all research interviews.

Para-verbal and non-verbal information, i.e., non-linguistic features that accompany speech, will be included in the full transcription. Para-verbal features of speech include voice inflections, accents, and whispers, as well as speech flow, hesitations, pauses, and silences. Non-verbal elements that accompanied and punctuated the speech will also be noted: smiles, laughter, pouting, crying, etc. These various gestures and mimics contribute to the subjective, conscious, or unconscious expression of feelings, opinions, and judgments of the interviewee.

The analysis of transcriptions will be carried out by the two researchers who will conduct the interviews. The researchers will analyze raw data to extract themes. They will take an inductive approach to identify patterns, highlighting topics that repeatedly emerge, characterizing them, and then organizing them into themes, which they will review and discuss to reduce the likelihood of personal bias and to ensure analytic robustness. Finally, they will summarize the themes to demonstrate the pattern of their findings. These analyses will then be collectively discussed by the multidisciplinary research team involved in the project, which included psychologists, sociologists, philosophers, and physicians. This interdisciplinarity will allow for a cross-referenced analysis, to reduce the subjectivity potentially associated with the researcher and his/her field of expertise and support the validity of the results.

The analysis of qualitative data (semi-structured interviews and observation notes) is consistent with the principles of the grounded theory: the data collected is used to construct an explanatory theory answering the initial question [36, 37]. Thematic analysis is carried out to form a thematic tree. The interpretation of this thematic tree allows for the emergence of concepts that constitute the comprehensive theoretical model for the situations under study [38].

## Discussion

Opposition and refusal of care are key concepts in clinical and ethical research, especially in older people. These concepts are frequently mentioned in studies involving older patients but have not been specifically defined. Our research protocol aims to investigate this field, through a pilot study using a reproducible methodology which is adapted to in-hospital services for short geriatric stays. Nevertheless, as this is a pilot study, it has the limitation of exploring opposition based on medical traces and comprehensive interviews carried out after this behavior occurs. In the long term, an exploration using ethnographic techniques would be preferable, based on the exploratory results of this pilot study.

Of course, the patient is free to make his/her medical decisions and the health professional has a responsibility to offer him various options and to accompany any decision made by the patient in the best possible way. Nevertheless, what justifies our study is the necessity of a better understanding, in the particular situation of neurocognitive diseases, of patients’ decision-making in cases where these decisions are not necessarily well informed due to cognitive disorders. It is essential to explore whether the perceived opposition behavior is enlightened, and requires a repositioning of the healthcare team to best support the patient’s wishes, or whether there is a lack of understanding of the situation, and therefore an uninformed opposition which must then impose a decision by derogation in accordance with ethical rules, following multidisciplinary meetings.

Indeed, the communication of a solid description and a thorough understanding of the opposition of hospitalized seniors to diagnostic and therapeutic medical procedures will provide professionals with results that can be used in their current practice related to the care and support of older people, while respecting their autonomy and wishes, to improve patient-centered care approach and to help managing patient’s best interest surrogate decision-making.

As such, the results of the present study can be used to develop training modules that will contribute to the prevention and support of situations involving opposition to diagnostic or therapeutic procedures.

